# 1 Supplementary Note

## 1.1 *Supplementary Note 1: Detailed Methodology and Results of Gut Microbiota Measures*

### 1.1.1 Methods

#### 1.1.1.1 DNA sequencing

Before sequencing, the quality of the DNA samples was evaluated using agarose gel electrophoresis and the quantity of the DNA was evaluated by Qubit 2.0 fluorometer quantitation. The genomic DNA was randomly sheared into fragments of around 350 bp. The fragmented DNA was used for library construction using NEBNext Ultra II Library Prep Kit for Illumina (New England Biolabs). The prepared DNA libraries were evaluated using Qubit 2.0 fluorometer quantitation and Agilent 2100 Bioanalyzer for the fragment size distribution. Quantitative real-time PCR (qPCR) was used to determine the concentration of the final library before sequencing. The library was sequenced using 2 x 150 bp paired-end sequencing on an Illumina platform.

#### 1.1.1.2 Gene catalogue and MGS definitions

We used a reference gene catalogue with 14 355 839 genes created from 21 598 human gut specimens (including 481 from infants, 9 428 publicly available metagenomes compiled from 43 countries,) and 3 567 publicly available genome assemblies) from isolated microbial strains. For taxonomic abundance profiling, we used Clinical Microbiomics HGMGS version HG4.D.2 metagenomic species (MGS), each represented by a set of genes with highly coherent abundance profiles and base compositions. The metagenomic species concept is described in .

To taxonomically annotate an MGS, we blasted its genes against NCBI RefSeq prokaryotic genomes (2022-01-19) and nt (2021-08-03) databases and used rank-specific annotation criteria. Specifically, we assigned a taxon to an MGS if at least M % of its genes were mapped to the taxon and no more than D % of its genes were mapped to a different taxon. We only considered blast hits with an alignment length  $\geq 100$  bp,  $\geq 50$  % query coverage and % identity  $\geq$  PID. Here we define: PID = (95, 95, 85, 75, 65, 55, 50, 45); M = (75, 75, 60, 50, 40, 30, 25, 20); and D = (10, 10, 10, 20, 20, 20, 20, 15) for subspecies, species, genus, family, order, class, phylum, and superkingdom, respectively. Finally, we processed each MGS with CheckM , and updated our annotation with the CheckM result if this resulted in a lower taxonomic rank.

#### 1.1.1.3 Sequencing data pre-processing

Raw FASTQ files were filtered to remove host contamination by discarding read pairs in which either read mapped to the human reference genome GRCh38 with Bowtie2 (v. 2.4.2, ). Reads were then trimmed to remove adapters and

bases with a Phred score below 20 using AdapterRemoval (v. 2.3.1, ). Read pairs in which both reads passed filtering with a length of at least 100 bp were retained; these were classified as high-quality non-host (HQNH) reads.

#### **1.1.1.4 Mapping reads to the gene catalogue**

HQNH reads were mapped to the gene catalogue using BWA mem (v. 0.7.17) (). An individual read was considered uniquely mapped to a gene if the mapping quality (MAPQ) was  $\geq 20$  and the read aligned with  $\geq 95$  % identity over  $\geq 100$  bp. However, if  $> 10$  bases of the read did not align to the gene or extend beyond the gene, the read was considered unmapped. Reads meeting the alignment length and identity criteria but not the MAPQ threshold were considered multi-mapped.

Each read pair was counted as either 1) uniquely mapped to a specific gene, if one or both individual reads were uniquely mapped to a gene, or 2) multi-mapped, if neither read was uniquely mapped, and at least one was multi-mapped, or 3) unmapped, if both individual reads were unmapped. If the two reads were each uniquely mapped to a different gene, the gene mapped by read 1 was counted but not the gene mapped by read 2. A gene count table was created with the number of uniquely mapped read pairs for each gene.

#### **1.1.1.5 MGS relative abundance calculation**

For each MGS, a signature gene set was defined as the 100 genes optimized for accurate abundance profiling of the MGS. An MGS count table was created by counting the number of reads uniquely mapped to the MGS signature genes per sample. An MGS was considered detected if reads from a sample uniquely mapped to at least three of its signature genes; measurements that did not satisfy this criterion were set to zero. Based on internal benchmarks, this threshold results in 99.6 % specificity. The MGS count table was normalized according to effective gene length and then normalized sample-wise to sum to 100 %, resulting in relative abundance estimates for each MGS.

Down sampled (rarefied) MGS abundance profiles were calculated by random sampling, without replacement, of a fixed number of signature gene counts per sample, and then following the procedure described above. In this study, 431127 signature gene counts were sampled.

#### **1.1.1.6 Functional annotation and profiling**

EggNOG-mapper (v. 2.0.1, Diamond mode),  was used to map each gene in the gene catalogue to the EggNOG (v. 5.0) orthologous groups database, resulting in EggNOG annotations for 79 % of genes and Kyoto Encyclopaedia of Genes and Genomes (KEGG) orthology (KO) database annotations for 46 % of genes. Functional potential profiles based on KOs were calculated as the proportion of all mapped reads that mapped to a given KO. KEGG modules (v. 78.2)  are defined as a set of KOs that enable a specific function or pathway. For each KEGG module, we define its corresponding FSG as the set of MGSs that include at least 2/3 of the genes that encode the proteins/enzymes that are needed to complete the functionality of the module. If a module has alternative reaction paths, only one of

these is required to be 2/3 complete. For modules with three or fewer steps, all steps are required to be comprised in the MGS.

The Gut Metabolic Modules (GMMs) are a set of 103 conserved metabolic pathways, each defined as a series of enzymatic steps represented by KO identifiers. We consider an MGS to contain a given module if the MGS includes genes annotated to at least 2/3 of the KOs needed to complete the functionality of the module. If a module has alternative reaction paths, only one of these is required to be 2/3 complete. For modules with three or fewer steps, all steps are required to be comprised in the MGS.

The Gut Brain Modules (GBMs) are a set of 56 microbial pathways for metabolizing neuroactive compounds (molecules that have the potential to interact with the human nervous system). Each GBM corresponds to a single neuroactive compound synthesis or degradation process by members of the gut microbiota and is defined as a series of enzymatic steps represented by orthologue group identifiers (KEGG, TIGRFAM, and eggNOG version 3.0 orthology databases in order of preference). We consider an MGS to contain a given module if the MGS includes genes annotated to at least 2/3 of the orthologous needed to complete the functionality of the module. If a module has alternative reaction paths, only one of these is required to be 2/3 complete. For modules with three or fewer steps, all steps are required to be comprised in the MGS. Since the GBMs were defined using eggNOG v 3.0, the seed orthologs for non-supervised orthologous groups were identified in eggNOG v 3.0 ([http://eggnoг.embl.de/version\\_3.0/](http://eggnoг.embl.de/version_3.0/)) and used to transfer these orthologs groups to the genes, within our gene catalogue, annotated with eggNOG v 5.0.

#### **1.1.1.7 Diversity estimates**

Alpha and beta diversity estimates were calculated from rarefied abundance matrices, created by random sampling of reads without replacement. Within each data type (e.g., gene, MGS), all samples were represented by the same number of informative sequencing reads: rarefaction of MGS abundance was performed by sampling only from reads mapping to MGS signature genes, and rarefaction of Kyoto Encyclopaedia of Genes and Genomes orthology (KO) abundance was performed by sampling only from reads mapped to a gene with an assigned KO. However, rarefaction of gene abundance was performed by sampling reads mapped to the entire gene catalogue. Alpha diversity was calculated as the number of entities detected (richness), as the Shannon index based on natural logarithm, or as Faith's phylogenetic diversity. Beta diversity was calculated as the Bray–Curtis dissimilarity and weighted UniFrac distances.

Pairwise comparisons of microbiota (dis)similarity were compared using the Mann-Whitney U test and verified by comparing the Mann-Whitney U test statistic obtained when analysing data with the original group labels to the test statistic distribution obtained by 1,000 group label permutations. The latter comparison was also performed using the Mann-Whitney U test.

Unless otherwise stated, permutational multivariate analysis of variance (PERMANOVA) tests were performed using the `adonis2` function from the `vegan` R package with 1000 permutations and `by = "margin"`, thus assessing the marginal effects of the terms (i.e. each marginal term analysed in a model with all other variables). Multivariate homogeneity of group dispersions was tested using the `betadisper` and `permutest` functions from the `vegan` R package with 1000 permutations and `type = "spatial median"`, which is an implementation of the PERMDISP2 procedure from^12. Distance-based redundancy analysis (dbRDA) tests were performed using the `capscale` function from the `vegan` R package with 1000 permutations and `"sqrt = T"` to prevent negative eigenvalues. With 1000 permutations, the lowest possible P value is  $1/1001 = 0.000999$ .

When performing statistical testing on multiple hypotheses, we used the Benjamini–Hochberg (BH) method to control the false discovery rate (FDR) at a level of 10%. Thus, of all the “statistically significant” associations we report in this context, we expect 10 % of these to be false associations (arising due to chance). When we report the “FDR-adjusted P value”, this is not a P value per se, but rather indicates the FDR at which a given hypothesis would be called significant using the BH method. FDR control was applied to each tested contrast individually, i.e., it accounts for multiple species being tested but does not account for multiple contrasts and across multiple analysed

visits. When we refer to a “nominal” P value, this indicates that the P value is not subjected to FDR control nor otherwise adjusted for multiple hypotheses.

Broad-sense heritability was determined with ACE model (from R package mets). The model estimates how much the phenotype variation stems from additive genetic effects (A), common environment (C) and unique environment for each twin (E). The model was fitted separately to the abundances of taxa found in more than 2 samples in each arm (*abundance* ~ 1) and used to extract broad-sense heritability.

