## 2.3 Supplementary Figure S3: Taxonomic overview at genus level per sample faceted by twin pair, and by study arm.

[figure not shown]

Bar plots display the relative abundance of the top 10 taxa with highest average abundance across all samples. Light grey (Other) indicates the total relative abundance of metagenomic species that are not in the top 10 most abundant taxa.

**2.4 Supplementary Figure S4: Bray–Curtis dissimilarities among samples stratified based upon whether they are from the same twin pair and from disparate twins pairs**

[figure not shown]

Bray-Curtis dissimilarity is a metric of beta diversity.

**2.5 Supplementary Figure S5: Mann-Whitney U test statistic distributions from comparing Bray–Curtis dissimilarities within and between twin pairs**

[figure not shown]

Original group labels (black line) and from 1,000 group label permutations (green). Left: Baseline, Right: End of study.

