## 2.7 *Supplementary Figure S7: Intra-twin pair Bray-Curtis dissimilarity between visits*

[figure not shown]

Intra-twin pair Bray-Curtis dissimilarity between visits (top left), visits by zygosity (top right), visits – monozygotic (bottom left), visits – dizygotic (bottom right)

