### ***d. Overall Improvement***

In addition to analysing the primary and secondary outcomes by arm, group-wide comparisons will be carried out for the following variables of interest: weight, BMI, SPPB

score, balance score, grip strength, chair rise time, gait speed, IPAQ MET minutes/week, IPAQ score, SNAQ score, CANTAB cognitive test results and serum metabolites.

Paired tests will be carried out to assess for differences between baseline and study end point, two sample t-tests for continuous variables (normally distributed), Mann-Whitney test for non-normally distributed continuous variables, and Pearson's chi-squared tests for categorical variables.

While there is no control group for these analyses, these will tell us whether the protein and exercise intervention that all twins will receive was beneficial for the aforementioned variables of interest, irrespective of gut microbiome modulation with a prebiotic food supplement. This analysis will also be repeated using two subgroups of interest, protein intake at baseline, and frailty index at baseline.

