## **1. Gut Microbiome Function and Composition**

Stool samples will be collected from all participants at the beginning and end of the study, via post. The DNA extraction will be carried out in our own laboratory, and then the extracted DNA samples will be sent to an external microbiome sequencing and bioinformatic company, who will carry out high-resolution shotgun metagenomics microbiome analysis of all samples. This includes full profiling of microbiota present (composition), functional species group association analysis, as well as measures of alpha and beta diversity for each individual sample.

Once the above information is available, statistical analysis will assess microbiota differences between the two study arms and between twin pairs. Microbiome composition will be analysed with respect to (1) species diversity, (2) compositional differences, (3) functional differences and (4) differences in abundance of taxa. All analysis will take a hierarchical approach; crude models assessing just the variable of interest (prebiotic supplementation), and models adjusted for key biological (age, sex, exercise etc.) and technical covariates (e.g., differences in library size) will be applied.

Differences in species diversity and richness will be compared between each study arm in regression analysis in crude and adjusted models. Distance matrixes characterise the inter-individual differences in microbiota composition; ordination analyses and permutational multivariate analysis of variance (PERMANOVA) will be used to understand differences in composition between each study arm.

ASVs will be collapsed to family, order, and phylum levels, with hierarchical models, adjusted for each potential mediator individually, then fully adjusted. All models will be adjusted for multiple testing.

All twins within each study arm will be used in paired and unpaired tests to assess if microbiota dissimilarity increased with differences in muscle strength, taking relevant covariates (including diet [HEI], BMI and frailty index) into consideration.

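### No test is named for the between-visit comparison of within-pair Bray-Curtis dissimilarity (Figure S7); the general Mann-Whitney rule, if applied there, ignores that the same twin pairs are measured twice

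*Combined protocol and SAP*

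**What the plan says.** Supplementary Note 1, section 1.1.1.8, states for dissimilarity values that "Pairwise comparisons of microbiota (dis)similarity were compared using the Mann-Whitney U test". The result is checked by comparing the observed statistic "to the test statistic distribution obtained by 1,000 group label permutations". No restriction of those permutations within twin pair is mentioned.

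The one analysis that the documents tie explicitly to this test is Supplementary Figure S5: "Mann-Whitney U test statistic distributions from comparing Bray–Curtis dissimilarities within and between twin pairs", shown separately for baseline and end of study.

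Supplementary Figure S7 is a different comparison. Its caption opens "Intra-twin pair Bray-Curtis dissimilarity between visits (top left), visits by zygosity (top right" and continues with separate monozygotic and dizygotic panels. It names no test, and the figure itself is not reproduced in the text available.

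Two passages in the SAP are adjacent. The section on gut microbiome function and composition says twins "will be used in paired and unpaired tests to assess if microbiota dissimilarity increased" with differences in muscle strength, without naming the tests. The section on overall improvement, which covers clinical, cognitive and metabolite variables, says: "Paired tests will be carried out to assess for differences between baseline and study end point, two sample t-tests for continuous variables". It goes on to list Mann-Whitney for non-normal data. That passage calls the comparison paired but lists two-sample tests.

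**The concern.** A twin pair has one within-pair distance at each visit. Baseline and study end in Figure S7 are therefore repeated measurements on the same pairs. Mann-Whitney assumes two independent samples. If a pair that is dissimilar at baseline tends to remain dissimilar at study end, the unpaired test leaves that shared variation in its error term. It then becomes conservative and loses power.

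Permuting visit labels freely across all the distances would not help, because it also breaks the link between a pair's two values.

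At stake is a real change in within-pair distance being reported as no change. One co-twin receives prebiotic and the other placebo, so that change is one informative view of whether the co-twins' microbiota diverged. The zygosity panels have the fewest pairs and would suffer most.

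**Working it through.** **Inputs from the documents.** Supplementary Table S1 gives 72 participants, 44 monozygotic and 28 dizygotic. That is at most 72/2 = 36 pairs, made up of 44/2 = 22 and 28/2 = 14. The number of pairs with stool data at both visits is not stated. The 0.05 significance threshold is from SAP section 7, Descriptive Statistics; a two-sided test is assumed.

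**Inputs that must be assumed.** The documents give no between-visit correlation of the distances (rho), no SD and no effect size. A shift of d = 0.5 SD is used for illustration, and rho is varied. The documents state no power for this comparison, so there is no figure of theirs to reproduce.

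**Approximation for type I error.** With equal SDs, the variance of the difference between visit means is 2(1 − rho)/n in SD units. The unpaired test assumes 2/n. Its nominal cut-off of 1.96 therefore acts as 1.96/√(1 − rho):

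- rho 0: 1.96, true error 5.0%
- rho 0.3: 1.96/0.837 = 2.34, about 1.9%
- rho 0.5: 1.96/0.707 = 2.77, about 0.6%
- rho 0.7: 1.96/0.548 = 3.58, about 0.03%

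**Approximation for power (n = 36, d = 0.5).** For the paired test the expected z is d√n/√(2(1 − rho)) = 3/√(2(1 − rho)). This is 2.12, 2.54, 3.00 and 3.87 at rho 0, 0.3, 0.5 and 0.7. Power, Φ(z − 1.96), is 56%, 72%, 85% and 97%. For the unpaired test power is Φ((2.12 − 1.96)/√(1 − rho)), that is 56%, 58%, 59% and 62%. These are mean-based values; rank tests run slightly lower.

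**Simulation with the rank tests themselves** (bivariate normal distances, 36 pairs, 4,000 replicates per setting, two-sided 0.05):

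| rho | Mann-Whitney type I error | Power, Mann-Whitney | Power, signed-rank | Loss (points) |
|---|---|---|---|---|
| 0 | 4.9% | 54% | 53% | none |
| 0.2 | 3.0% | 53% | 62% | 9 |
| 0.3 | 2.1% | 54% | 66% | 12 |
| 0.5 | 0.6% | 54% | 82% | 28 |
| 0.7 | 0.2% | 56% | 96% | 40 |

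Separate runs gave losses of 12 to 14 points at rho 0.3, 25 to 28 at 0.5 and 39 to 41 at 0.7, and a type I error of 0.1% to 0.2% at rho 0.7. Using a bounded 0-to-1 scale in place of the normal changed little.

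**Smaller numbers.** With 30 pairs the powers are 45% v 59% (rho 0.3), 45% v 74% (0.5) and 44% v 92% (0.7). At rho 0.5 they are 30% v 59% for 22 monozygotic pairs and 15% v 39% for 14 dizygotic pairs.

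**Negative correlation.** At rho −0.2 Mann-Whitney shows 53% power against 46%, but its type I error rises to 6.6%, so that apparent gain is not valid.

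**The case against.** The strongest reply is that no document says Mann-Whitney was used to compare visits. The methods sentence, with its 1,000 label permutations, matches Figure S5, where distances within pairs are set against distances between pairs at one visit. Figure S7 cannot be seen: a test may be printed on its panels, or it may be purely descriptive. Figure S6 describes a paired comparison of taxa between the same two visits, so pairing was recognised in the neighbouring analysis. In the panel split by zygosity, a contrast of monozygotic with dizygotic pairs would involve disjoint groups, for which Mann-Whitney is suitable.

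Most of this stands. A reader might infer that Figure S7's p-values are known to be too large; the documents do not support that, since the test used there is not stated. A reader might also infer that Mann-Whitney is the only test named for microbiota dissimilarity. It is not: the same section reports that "permutational multivariate analysis of variance (PERMANOVA) tests were performed using the" adonis2 function, and also names betadisper with permutest, and distance-based redundancy analysis.

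The reply does not remove the point. Those other methods address composition or group dispersion and do not compare one distance per pair across two visits. The Mann-Whitney sentence is general and makes no exception for visits. The SAP's habit of calling baseline-to-end tests paired while listing two-sample tests makes an unpaired application plausible, though it does not prove one.

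**Conclusion.** The point holds conditionally. Mann-Whitney is the only test named for comparing pairwise dissimilarity values, and no test is named for Figure S7. Read literally, the general rule gives an unpaired test for data that are paired by design.

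A statement that much of the power is lost would go too far without the correlation. With 36 pairs and a 0.5 SD shift the loss is nil at rho 0, about 13 points at 0.3, about 27 at 0.5 and about 40 at 0.7. For positive rho the fault is conservative and creates no excess false positives. Because the signed-rank test costs almost nothing at rho 0 and keeps its level throughout, the paired choice does not depend on knowing rho.

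Nor is this a flaw in the trial's main inference. Change over time in within-pair distance is a before-after contrast: drift in either twin alters it, and both twins receive protein and exercise advice. Gut microbiome measures are secondary outcomes. Neither chair rise time nor the randomised comparison between arms is affected. It is a minor correction.

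**What to change.** Name the test for Figure S7. For the between-visit comparison of intra-pair dissimilarity, compute each pair's study-end value minus its baseline value and test these changes with a Wilcoxon signed-rank test. A permutation that swaps visit labels only within a pair is an alternative. Do this overall and separately for monozygotic and dizygotic pairs, and report the median change with its confidence interval and the number of pairs contributing. Keep Mann-Whitney for disjoint groups of pairs, such as the change in monozygotic against dizygotic pairs. If a paired test was already used, only the methods sentence and the caption need amending.

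The cost is a line of text and, if needed, a re-run on distances that already exist. Pairs lacking a sample from either twin at either visit drop out of the paired test, so that number should be stated.

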## **7. Statistical Analysis**

### ***a. Descriptive Statistics***

All outcomes will be presented using descriptive statistics; normally distributed data by the mean and standard deviation (SD) and skewed distributions by the median and interquartile range (IQR). Binary and categorical variables will be presented using counts and percentages. P values of  $\leq 0.05$  will be considered sufficient to reject the null hypothesis.

Outliers will be assessed by examining plots and checked for possible erroneous entry. Where necessary, results with and without outliers will be compared to assess for discrepancies in the results, and this will be discussed if found to be discrepant.

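### The twin-similarity check tests one U statistic against 1,000 permuted ones with an unneeded second Mann-Whitney test of unstated version; the direct permutation p-value should be reported instead

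*Combined protocol and SAP*

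**What the plan says.** Supplementary Note 1, section 1.1.1.8, describes two steps for pairwise microbiota dissimilarity.

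- **Step 1.** The groups of dissimilarities are compared by Mann-Whitney. Supplementary Figure S5 shows which groups these are: "Mann-Whitney U test statistic distributions from comparing Bray–Curtis dissimilarities within and between twin pairs".
- **Step 2.** The result is checked by comparing "the Mann-Whitney U test statistic obtained when analysing data with the original group labels" with the "test statistic distribution obtained by 1,000 group label permutations". On this step the section says: "The latter comparison was also performed using the Mann-Whitney U test".

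The Figure S5 caption shows the same layout, with one black line for the original labels against the permuted values, at baseline and at end of study.

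The section does not say whether the second test is exact or approximate, or one- or two-sided. It gives no p-value for it, and does not say what unit the labels were permuted over. The next paragraph, on PERMANOVA, dispersion tests and dbRDA, gives the smallest p-value available from 1000 permutations as 1/1001 = 0.000999. The SAP's general rule (Descriptive Statistics) is that p of 0.05 or less "will be considered sufficient to reject the null hypothesis". Section 1.1.1.8 uses a 10% false discovery rate where several hypotheses are tested.

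**The concern.** A permutation test needs no further test. The permuted statistics form the null distribution, and the p-value is the rank of the observed statistic within it. Feeding that one statistic and its 1,000 permuted counterparts into a Mann-Whitney test treats the observed value as a sample of size one. In the usual large-sample form, the uniform distribution of a single rank is then replaced by a normal curve, which is a poor substitute.

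This matters because step 1 cannot stand as the test of record. It treats pairwise distances as independent, although every sample contributes to many of them. The permutation step is where that dependence could be handled properly. If its result is passed through an approximation with a high floor, a clear finding of twin similarity could be reported as not confirmed at 5%.

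**Working it through.** **Inputs.** n1 = 1 observed U per visit and n2 = 1,000 permuted U (section 1.1.1.8; Figure S5). The SAP threshold is 0.05. There are 72 participants (Supplementary Table S1).

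**The stated permutation floor.** 1/(1000 + 1) = 0.000999. This reproduces the figure given for PERMANOVA, dispersion and dbRDA.

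**Floor of the second Mann-Whitney test.** Take the most extreme case, with the observed value outside all 1,000 permuted values (second-stage U = 0).

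- Mean = n1·n2/2 = 1 × 1000/2 = 500.
- SD = √(n1·n2·(n1 + n2 + 1)/12) = √(1 × 1000 × 1002/12) = √83,500 = 288.96.
- Without continuity correction: z = 500/288.96 = 1.730.
- With continuity correction: z = 499.5/288.96 = 1.729.

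| Version | Smallest one-sided p | Smallest two-sided p |
|---|---|---|
| Normal approximation, no correction | 0.0418 | 0.0836 |
| Normal approximation, corrected | 0.0419 | 0.0839 |
| Exact | 1/1001 = 0.000999 | 2/1001 = 0.0020 |

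More permutations do not help the two-sided approximation: z tends to √3 and p to 0.0833.

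**Which version is likely.** The section names R packages. R's `wilcox.test` with default settings uses the corrected approximation for a group of 1,000 and returns 0.0839; with `exact=TRUE` it returns 0.0020. This makes the approximation likely, but the documents do not state it.

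**Dependence in step 1.** Assume all 72 samples are available at a visit.

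- Distances: 72 × 71/2 = 2,556.
- Within pair: 36. Between pairs: 2,556 − 36 = 2,520.
- Each sample enters 71 distances.

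The documents give no count of analysed stool samples per visit. With 30 complete pairs, for comparison, there would be 60 × 59/2 = 1,770 distances, with each sample in 59. The dependence is present either way.

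Mann-Whitney takes its variance as if the within-pair distances were a simple random draw from all distances. In fact each sample appears in exactly one within-pair distance, so sample-level variation partly cancels. In an illustrative null simulation (Bray–Curtis on random compositions, pair membership permuted), the SD of the step 1 z-statistic was 0.32 to 0.81 instead of 1. The shortfall depends on the compositions assumed, and other choices bring it nearer to 1. In those settings the step 1 p-value was conservative.

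**What is permuted.** If labels were shuffled over individual distances, the permuted U values follow the same independent-draw distribution that step 1 already assumes, and the dependence stays unaddressed. If twin-pair membership was shuffled over samples, the permuted U values carry the dependence and their distribution is a sound reference.

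**The case against.** The strongest objection is to a reading that the working invites: that the check can never confirm twin similarity, because its p-value is always above 0.08. The documents do not support that. The floor of about 0.084 belongs to the two-sided normal approximation, not to the Mann-Whitney test. The exact version reaches 0.002. A one-sided version, natural for a hypothesis that twins are more alike, reaches 0.042 even under the approximation. If the section's 10% false discovery rate were applied to the two visits, two values of 0.0839 would also pass, since the larger adjusted value is 0.0839 × 2/2 = 0.0839. Figure S5 also lets a reader place the observed U directly in the permuted distribution. All of this stands.

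A reader might also infer that the matched design rests on this check. It does not. Protocol 10.1 and the SAP's Trial Design section justify pairing by age, sex, early environment, genetics and socioeconomic status. The twin-pair random effect in the primary model is prespecified, and the microbiome correlations in Figures S8 to S10 are adjusted for twin pair regardless of this result.

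Finally, the sentence about the latter comparison could mean only that the permuted-label analyses also used Mann-Whitney. That is possible but less natural: the comparison just described is the observed statistic against the permuted distribution. On that reading no p-value for the check is defined at all, and the same fix applies.

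What the objection leaves standing is that the second test is redundant, its version is unstated, the unit of permutation is unstated, and the step 1 p-value ignores dependence.

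**Conclusion.** The concern holds in a limited form. As described, the verification adds a Mann-Whitney test of one value against 1,000 where the permutation p-value is already available. Run as a two-sided normal approximation, that test cannot go below about 0.084 and so cannot meet the SAP's 0.05 rule. Run exactly, or one-sided, it can. The documents do not say which was used, so failure of the check is a possibility that depends on a software setting and is not established.

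The step 1 p-value is not calibrated and should not be the test of record. The illustration suggests that it errs on the conservative side, so the twin-similarity conclusion may well survive.

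This rests on the natural reading of the section together with the Figure S5 caption. The counts of 2,556 and 71 further assume complete stool samples at a visit. Severity is minor: the primary outcome and the arm comparisons are unaffected.

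**What to change.** In section 1.1.1.8, delete the second Mann-Whitney test. For each visit, report p = (1 + number of permuted U at least as extreme as the observed U)/1001 as the test of record, in place of the step 1 p-value. State the direction; the floor is 0.000999 one-sided, or 0.0020 if doubled. State that twin-pair membership is permuted across samples, not the within/between labels on individual distances, and give the number of samples and complete pairs at each visit.

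If pair membership was already what was permuted, the cost is one count per visit from statistics in hand. If labels on distances were permuted, a short re-run of 1,000 permutations per visit is needed. No new data are required either way.
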